## Assignment of interventions

### Sequence generation {16a}

A randomisation list will be prepared independently by statisticians at the Coordinating Centre using a computer-generated simple randomisation protocol and a 1:1 allocation sequence. A generated randomisation list will be delivered to the investigational product manufacturer (ChemiPharm). Both BioBlock and placebo spray vials have an identical appearance with no treatment allocation displayed. All vials have permanent (non-removable) labels with identifiable serial numbers (Table 2).

**Table 2 Tab2:** Table to the general practitioner, prepared by the trial statistician

Cluster number	Serial numbers on the vials					Group allocation*
1	TL001	TL001	TL001	TL001	TL001	Placebo
2	TL002	TL002	TL002	TL002	TL002	Placebo
3	TL003	TL003	TL003	TL003	TL003	Active
4	TL004	TL004	TL004	TL004	TL004	Placebo
5	TL005	TL005	TL005	TL005	TL005	Active
6	TL006	TL006	TL006	TL006	TL006	Active
7	TL007	TL007	TL007	TL007	TL007	Active

*Information shielded from the study staff

### Concealment mechanism {16b}

The allocation sequence will be held independently of the research team at GP clinics.

### Implementation {16c}

Once an index participant has completed baseline assessments, the GP will perform the randomisation utilising the centrally held database. Clusters are assigned to a study group sequentially following the randomisation list, and sprays dispensed by the GP. For each cluster to be randomised, five vials of spray are prepared with a unique serial number. GP clinics will use a courier service to deliver assigned investigational products to participating households. The number of vials delivered to a household will depend on the number of consenting study subjects in the household. The vials also have a dedicated place for user name printing (to individualise spray vials).

### Who will be blinded {17a}

The spray vials are blinded at the site of manufacture. The RCT is triple-blind, in which the GP, the study participants and the assessor (at the SARS-CoV-2 RNA testing laboratory) are blinded to the actual spray allocated to the patient. There are no pre-determined situations in which blinding should be broken.

### Procedure for unblinding if needed {17b}

Unblinding will be needed in the event of medical emergencies or serious medical conditions that occur while a participant is taking part in the study whereby the participant may not be able to be treated adequately unless doctors know which treatment they have been receiving. Given the nature of the experimental spray and placebo, we consider this to be an unlikely event. In case of the need for unblinding, the Coordinating Centre needs to be contacted.

## Data collection and management

### Plans for assessment and collection of outcomes {18a}

Assessments will be completed at baseline, after use of the spray (at day 14) and at day 21 (for index cases and infected household members) on follow-up. Data will be collected from the results of an interview and respiratory specimen testing (Table 1).

All interviews will be administered by telephone. Enrolled index cases and SARS-CoV-2 RNA-positive household contacts will complete four phone interviews, including the enrolment interview (day 1) and follow-up interviews on days 7, 14 and 21 of enrolment. Enrolled SARS-CoV-2 RNA-negative household contacts will complete three phone interviews, including the enrolment interview (day 1) and follow-up phone interviews on days 7 and 14.

Data collection questionnaires are based on the WHO household transmission investigation protocol for coronavirus disease 2019 (COVID-19) [16]. We will seek information on the sociodemographic characteristics of participants/households; dwelling type and size; household structure; comorbidities; smoking history; household, occupational and community-related exposures; and utilisation of individual prevention measures. At follow-up, we will assess intervention adherence and occurrence of potential side effects. A visual analogue scale (VAS) for measuring nasal spray use adherence will be used [21]. All responses will be stored in a secure Web platform.

The assessment will include interviews administered remotely via a video-conferencing application or by telephone and Web-based testing referral.

### Specimen collection

Index case COVID-19 confirmatory test results are obtained in routine care at the general practice and the date of testing will be retrieved from participating GPs.

GPs will refer participating household members for SARS-CoV-2 RNA testing to the routine testing sites. In this study, nasopharyngeal swabs will be used for SARS-CoV-2 RNA testing.

Laboratory assessment: The nasopharyngeal samples collected will be tested for SARS-CoV-2 RNA by quantitative reverse-transcriptase–polymerase-chain-reaction (RT-PCR) at the SYNLAB Laboratory, a private medical laboratory company (SolGent DiaPlexQT Novel Coronavirus (2019-nCoV) Detection Kit CE-IVD). Viral RNA from all samples will be isolated within 24 h. The laboratory will provide daily updates to the GP clinics and study Coordinating Centre research staff.

### Plans to promote participant retention and complete follow-up {18b}

Research staff at GP clinics will maximise engagement with participants and facilitate their completion of follow-up assessments. This includes flexibility around the timing of assessments and reminders of missed assessments.

### Data management {19} and confidentiality {27}

Staff at GP clinics will receive training in all aspects of data collection and management. Screening logs and enrolment (identification) logs will be kept at the two GP clinics in locked cabinets within a secured room. All participants (index cases and their household members) will be given a unique study participant identification number. A Web-based electronic data capture system will be designed using REDCAP software. Data will be entered under identification number onto this centrally held database stored on the servers based at the Coordinating Centre. Access to the database will be controlled with unique usernames and encrypted passwords and restricted to members of the research team and external regulators if requested. The servers are protected by firewalls and maintained according to best practice.

The database and associated code lists have been developed by the study coordinators (research team) at the University of Tartu. The database software (REDCAP) provides a number of features to help maintain data quality, including maintaining an audit trail, allowing custom validations on all data, allowing users to raise data-query requests and search facilities to identify validation failure/missing data.

## Statistical methods

We will report participant flow in accordance with the CONSORT principles, with the 2012 extension for reporting cluster trials [22]. Descriptive statistics will be used to summarise assessments of recruitment and completion of the study.

### Statistical methods for primary and secondary outcomes {20a}

Our primary analysis will be a modified intention-to-treat analysis (excluding the clusters with no SARS-CoV-2-negative close contacts at baseline from the analysis). We will randomise clusters (households) prior to knowing the SARS-CoV-2 RNA status of close contacts of index patients (i.e. randomisation will be done before obtaining laboratory information on the SARS-CoV-2 status of household contacts). We argue that given the triple-blinded character of the study, post-randomisation exclusion of clusters with no SARS-CoV-2-negative contacts (exclusion due to excessively broad eligibility criteria [23]) will be random and will not lead into bias [24, 25].

A secondary analysis will be on the intention to treat, including all patients randomised into the study.

BioBlock effectiveness will be estimated using Cox regression (BPE = 1 − hazard ratio [HR]) or Poisson regression (BPE = 1 − rate ratio [RR]). Follow-up will be from baseline to the earliest of outcome or study exit. Cluster robust variance estimator is used to account for clustering.

Both unadjusted and adjusted estimates of BioBlock effectiveness will be presented. Adjustment will be made in the multivariable regression model for main potential confounders (age, symptomatic index cases; household size; sharing bedroom) [26, 27].

Baseline characteristics on family and individual levels will be characterised by descriptive statistics. In case of serious imbalances in variables that are not pre-specified for adjustment, additional sensitivity analysis with additional predictors will be performed.

Number (%) of adverse events and hospitalizations per group are reported. Mean (sd) and median (IQR) duration of symptoms is calculated and compared between groups using linear regression with cluster robust standard errors in case of correlated observations or *t*-test or Wilcoxon rank-sum test.

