## Introduction

### Background and rationale {6a}

On 11 March 2020, the World Health Organization (WHO) characterised COVID-19 — a condition caused by the severe acute respiratory syndrome coronavirus 2 (SARS-CoV-2) — as a pandemic. By the mid of 2021, the world is approaching the milestone of four million COVID-19 deaths [1].

Control measures (non-pharmaceutical interventions, including business and school closures, restrictions on movement, total lockdowns, social distancing) have been widely implemented to contain the spread of SARS-CoV-2 and have been effective in curbing the COVID-19 epidemic but do not represent desirable nor sufficient long-term strategies. Multiple vaccines are already at our disposal, but these vaccines will not be sufficient to immunise the majority of the seven billion people on the planet (the volumes needed, costs, cold chain requirements and suboptimal acceptance consist just some of the barriers) [2, 3].

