### Eligibility criteria {10}

#### Inclusion and exclusion criteria

Newly laboratory-confirmed cases of COVID-19, aged 16 years or older, with at least one additional household member eligible for participation will be recruited. Household members are eligible for recruitment if they are aged 16 years or older.

Individuals excluded include those who do not live in a household; are pregnant; are receiving active cancer or biological treatment or medications administered by inhalation, or via the naso- and oropharyngeal route; and recovered from confirmed COVID-19 and patients with any organ transplant and with asthma or with known allergies to BioBlock components.

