## Trial status

Protocol version 2.0 (August 27, 2021). The recruitment will begin in June 2021 and will be completed by December 31, 2021.

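### The pre-specified adjustment set leaves out COVID-19 vaccination, which gives up some precision and leaves chance imbalance to an undefined sensitivity analysis, without biasing the comparison

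*Protocol article*

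**What the plan says.** The protocol article, Statistical methods for primary and secondary outcomes {20a}, promises unadjusted and adjusted estimates of BioBlock effectiveness and lists the adjustment variables: "Adjustment will be made in the multivariable regression model for main potential confounders (age, symptomatic index cases; household size; sharing bedroom". The list is closed: nothing marks it as an example or defers it. For any other variable the same section offers one provision: "In case of serious imbalances in variables that are not pre-specified for adjustment, additional sensitivity analysis with additional predictors will be performed". It does not say what counts as serious.

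Four other places bear on the point:
- Background and rationale {6a}: "Multiple vaccines are already at our disposal".
- Trial status: "The recruitment will begin in June 2021 and will be completed by December 31, 2021".
- Inclusion and exclusion criteria: people who have "recovered from confirmed COVID-19" are excluded. Vaccinated people are not mentioned.
- Sequence generation {16a}: a "computer-generated simple randomisation protocol and a 1:1 allocation sequence", with the household as the unit and no stratification.

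Vaccination is not named in Table 1 or in the list of interview topics under {18a}.

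**The concern.** The eligibility rules remove one source of prior immunity, past confirmed infection, and leave the other, vaccination, in the trial population without a place in the design or the pre-specified model. The protocol itself treats four predictors of household infection as important enough to name in advance. Vaccination was foreseeable on the protocol's own account of when the trial runs.

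Two things are at stake. The first is precision: a prognostic covariate left out of the model leaves explainable variation in the treatment estimate. The second is the credibility of the one realised trial. If the arms happen to differ in vaccination, the planned adjusted estimate will not correct for it. The only recourse is then an analysis chosen after the imbalance has been seen, and readers may fairly discount that.

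**Working it through.** **Inputs from the protocol article.** Sample size {14}: 124 clusters, average size two, ICC 0.0170, coefficient of variation of cluster size 0.50, infection rate 30%, risk halved, 80% power, alpha 0.05. Section {20c}: two-sided test.

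**Assumed inputs, because the documents give none.** 50% of households are vaccinated, with everyone in a household sharing the same status. Vaccination lowers a contact's risk by e = 30%, 50% or 70%.

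**1. The plan's own figure.** 30% against 15%, two-sided 0.05, 80% power (pooled variance, no continuity correction) needs 121 contacts per arm. The design effect is 1 + ((0.50² + 1) × 2 − 1) × 0.017 = 1.0255. Then 121 × 1.0255 = 124.1 contacts per arm, or 62.0 clusters of two, which gives 124 in total. Power at 62 clusters per arm is 80.1%. The figure reproduces with two analysed contacts per cluster, so the checks below use that number.

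**2. Size of chance imbalance.** The SD of the arm difference in the vaccinated proportion is sqrt(2 × 0.25 / 62) = 0.090, and 1.96 × 0.090 = 0.176. One SD is thus 9 percentage points and the 95% limit is about 18. Simulated simple randomisation of 124 households gives an SD of 0.089. It puts the chance of a difference of at least 10 points at 25% (23% to 25% for coverage of 30% to 70%), and of at least 15 points at 9% (7% to 9%).

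**3. Effect on a null relative risk.** With p1 and p0 the vaccinated proportions in the two arms, the apparent RR is (1 − e·p1) / (1 − e·p0). One SD gives p1 = 0.545 and p0 = 0.455. The 95% limit gives 0.588 and 0.412.

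| Risk reduction e | RR at 9 points | RR at 18 points | ICC implied |
|---|---|---|---|
| 30% | 0.97 | 0.94 | 0.013 |
| 50% | 0.94 | 0.89 | 0.048 |
| 70% | 0.91 | 0.83 | 0.124 |

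Imbalance in the other direction is equally likely and gives the reciprocals.

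**4. Consistency with the planned ICC.** The last column is the ICC that household vaccination alone would create at a mean risk of 30%: (half the risk difference)² / (0.30 × 0.70). For e = 50% the risks are 0.40 and 0.20, so 0.10² / 0.21 = 0.048. Only the 30% scenario fits within the planned 0.017. The other two need about 3 and 7 times as much.

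**5. Benchmark.** With 124 contacts per arm at 30%, the SE of log RR is sqrt(2 × (0.7 / 0.3) / 124 × 1.0255) = 0.196. Under no effect, 95% of estimates lie between exp(−0.385) = 0.68 and exp(0.385) = 1.47. Every shift in the table is inside that range.

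**6. Value of adjustment.** Poisson regression with cluster-robust variance was simulated for 124 clusters of two, with 1,500 trials per scenario, without and with household vaccination as a covariate.

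| e | Power at true RR 0.5, without | with | Type I error, without | with |
|---|---|---|---|---|
| 30% | 78.3% | 79.1% | 4.8% | 4.6% |
| 50% | 79.7% | 82.9% | 5.5% | 4.7% |
| 70% | 77.7% | 83.7% | 4.1% | 4.5% |

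The mean log RR under no effect is within 0.01 of zero in every case. The Cox option in {20a} was not simulated.

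**The case against.** The best defence is that nothing here is invalid. Section {20a} names covariates with cited support, reports both unadjusted and adjusted results, and provides for serious imbalance. Chance imbalance is already part of what the confidence interval allows for. That stands, and it limits the point to precision and conditional balance. It does not make the fallback equivalent to pre-specification: the fallback has no threshold, it is triggered by the data, and it leaves the planned adjusted estimate unchanged.

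The 18-point figures can also be called a worst case. They combine the 95% limit with status shared by the whole household. If contacts' statuses were independent, the limit would be 1.96 × sqrt(2 × 0.25 / 124), about 12 points. This too stands, which is why the one-SD figures come first.

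A reader might infer several stronger claims that the documents do not support:
- *The primary comparison is biased or its error rate inflated.* Randomisation prevents the first on average, and the simulation shows type I error of about 4% to 6% either way.
- *Vaccination is not recorded.* The article gives only broad questionnaire topics, including individual prevention measures. The questionnaire is not shown, so this cannot be judged.
- *Vaccination is known to be a major predictor in this population.* No coverage or effect is given, so its strength is an assumption throughout.
- *The hospital-admission analysis has the same gap.* Section {20a} reports admissions as numbers and percentages per group, so there is no model to which a covariate could be added.

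**Conclusion.** The point holds as a moderate one, a cheap improvement rather than a correction of an error. The closed covariate list omits a predictor that was foreseeable from the protocol's own timing, background and eligibility rules, in a trial with no stratification and about 62 clusters per arm.

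Under the assumed coverage and effects, a typical imbalance would move the estimate by about 3% to 9%, and one at the 95% limit by about 6% to 17%. The upper ends depend on household clustering well above the planned ICC. Pre-specified adjustment would gain roughly 1 to 6 points of power. That is useful in a trial sized for 80%, but it does not decide whether the trial is valid. If vaccination proved only weakly related to infection, the gain would be near the bottom of that range.

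**What to change.** Before unblinding, amend {20a} so that the vaccination status of the contact and of the index case, both as at enrolment, joins the pre-specified covariates of the adjusted primary model. Do the same for the symptom-duration comparison where linear regression is used.

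First check whether the questionnaire already captures vaccination. If it does, only the covariate list changes. If it does not, add a question to the enrolment interview and, for households still in follow-up, to the next scheduled call, asking about status at enrolment rather than at the time of the call.

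The cost is one or two questions and one or two model terms. Households that have finished their calls (day 14 for uninfected contacts, day 21 for infected participants) will have some missing values. The amendment should say how these are handled so that such contacts stay in the adjusted analysis, because the missing-data section {20c} addresses missing outcomes only.

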### Interim analyses {21b}

There are no planned interim analyses.

### Statistical methods to handle missing data {20c}

Every effort will be made to follow up all participants for research assessments. All models will be estimated using maximum likelihood estimation which allows for missing outcome data under the missing-at-random assumption. Sensitivity analyses with worst-case and best-case scenarios are performed.

Statistical analyses will be conducted using Stata software (version 15, StataCorp, College Station, USA). A two-sided *p* value of less than 0.05 will be considered to indicate statistical significance.

### Availability of data and materials {29}

The individualised datasets generated and/or analysed during the current study will not be available. The corresponding statistical code will be available from the research team upon reasonable request, subject to review, following the publication of trial results.

## Oversight and monitoring

### Coordinating Centre {5d}

Research staff at the University of Tartu provide scientific support and oversight and will coordinate all trial activities. The research programme development, design and implementation will be managed by the principal investigator and the co-authors in consultation with GP clinic consultants and experts from the testing laboratory. A dedicated trial coordinator will assist in the day-to-day management of the project at the GP clinics.

### Composition of the data monitoring committee, its role and reporting structure {21a}

As the trial has been assessed to pose a minimal risk to participants, a formal data monitoring committee is not required. The study will be monitored for quality, contextual appropriateness and regulatory compliance. A trial coordinator will monitor the intervention through weekly visits to GP clinics.

### Adverse event reporting and harms {22}

The occurrence of any harms and adverse events will be monitored actively and systematically, following guidance from Consolidated Standards of Reporting Trials (CONSORT). Any adverse event affecting participants on the study observed by GPs or the trial coordinator will be assessed by the principal investigator to decide whether additional investigation, or a modification of the intervention, may be indicated.

### Frequency and plans for auditing trial conduct {23}

The researchers, sponsor and developer will meet regularly (bi-weekly during the initial phase) to monitor progress and conduct of the trial. The main areas of review are (1) ethical review board oversight and consent contents, (2) handling of investigational devices (active and placebo sprays) and (3) patient case review. Auditing visits will be held pre-study (before participant recruitment), after initiation, during the course of study and at close-out.

### Plans for communicating important protocol amendments to relevant parties (e.g. trial participants, ethical committees) {25}

Protocol amendments will be communicated as, and if, required by the principal investigator.

Ancillary and post-trial care {30} will be investigating GP discretion and done according to the Estonian treatment guidelines/clinical routine.

### Dissemination plans {31a}

It is intended that the results of the study will be reported and disseminated at international conferences and in peer-reviewed scientific journals and will be made available to participants and clinical teams in an accessible format and on the study website. The results of the research are expected to be submitted for publishing 6 months after the end of trial data collection. All participants will be fully anonymised in any reporting. In addition, we will produce a short report of findings for each participating GP clinic.

## Discussion

Based on the opinion of more than 100 prominent scientists, coronavirus cannot be eradicated and will become endemic — meaning that it will continue to circulate in pockets of the global population for years to come [28]. A large portfolio of evidence-based prevention and treatment strategies are needed to meet the highly versatile needs of populations.

In most countries, those with confirmed or suspected infections are requisitioned to isolate at home, putting other members of their household at risk of infection. Therefore, in parallel to the need of household transmission prevention measures, households also present as a good model for infection transmission studies, allowing for the testing of several close contact transmission prevention study hypotheses (including infectiousness, susceptibility) (Fig. 1) [29].

